### Clinical (primary) outcomes

Clinical outcomes to determine the intervention effectiveness of the Resource will be retrieved from a standardized 24-h period from medical records of hospitalized infants at baseline (T1) and at six (T2) months after randomization for both groups (See Table 1), including:
The proportion of infants in the NICU who have documented procedural pain assessment using a valid pain measure (e.g. Premature Infant Pain Profile – Revised [25], Neonatal Infant Pain Scale [26], Behavioral Indicators of Infant Pain [27], among other valid measures each unit my use as part of their pain practices);The proportion of infants in the NICU who have documented procedural pain management with evidence-based pharmacological or physical interventions documented;Total number of documented painful procedures (e.g. heel lance, arterial puncture, eye examination) per infant in the NICU.

**Table 1 Tab1:** Study primary, secondary, and other outcomes

Primary outcomes	Description	Measure/Metrics	Timepoints for data collection
Proportion of infants with procedural pain assessed	Total number of pain assessments performed using a valid pain measure and documented over a 24-h period (i.e. midnight to midnight)	Whether or not an infant’s procedural pain was assessed with a valid pain measure [7]	T1, T2 (for both groups)
Proportion of infants with procedural pain management	Total number of pain management interventions (pharmacologic and/or non-pharmacologic) implemented and documented over a 24-h period (i.e. midnight to midnight)	Whether or not an infant received pharmacologic (e.g. sucrose, opioids, acetaminophen) and/or non-pharmacologic (e.g. breastfeeding, skin-to-skin contact, non-nutritive sucking) interventions for procedural pain [7]	T1, T2 (for both groups)
Frequency of painful procedures	Total number of painful procedures documented in clinical charts over a 24-h period (i.e. midnight to midnight)	Absolute number of painful procedures per infant documented in a 24-h period [7]	T1, T2 (for both groups)
Secondary outcomes	Description	Measure/Metrics	Timepoints for data collection
Feasibility	The extent to which the Resource was successfully implemented in terms of ease of use and time [10, 15]	Focus group. A semi-structured interview guide was developed according to CFIR constructs on intervention characteristics [9] and has been pre-tested in a usability study [12]	T2 (for INT group)

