Implementation fidelity	The degree to which the Resource is used by a team as prescribed or intended [10, 15]	Progression through the Resource, which includes completion of each of the seven steps, completeness of included information will be considered the metric for fidelity. These data will be captured from the backend of the website at completion of using the Resource	T2 and T3 (for INT and SP groups, respectively)
Implementation costs	The financial and time cost to implement the Resource [10]	Data on human resources (time spent on orientation session, navigation through the Resource, meeting among team members, implementation of the Resource either individually or in group); space (for meetings and education sessions, for example); equipment (e.g. laptop); materials (e.g. printing materials), and other related expenses. These data will be captured from the backend of the website.	T2 and T3 (for INT and SP groups, respectively)
Reach	The integration of a KT strategy within a service setting and its subsystems [15]	Proportion (%) of NICU staff who receive a KT strategy (selected from the Resource) divided by the total number of NICU staff expected to receive the service [15]. These data will be captured from the backend of the website	T2 and T3 (for INT and SP groups, respectively)
Sustainability	The extent to which the newly implemented Resource is maintained or institutionalized within a service setting’s ongoing, stable operations [10, 15]	Maintenance of intervention effectiveness over time. These data will be captured from clinical charts over a 24-h period. Duration (in months) that NICU continues to use the ImPaC Resource with fidelity. These data will be captured from the backend of the website	T3 (for INT group), and T4 (for both groups)
Other data	Description	Measure	Time points for data collection
Context evaluation by [1] staff nurses and [2] change team members	Factors describing the local organizational context	Alberta Context Tool (ACT) [14]. This is a reliable and valid tool that determines which elements of context facilitate and/or hinder successful KT outcomes [16]. It additionally captures a brief section on demographic data in addition to the 56 items and 5-point Likert scale answers for each item)	T1 (for staff nurses of both groups) and at commencement of the Resource (for both groups)

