### Implementation (secondary) outcomes

Implementation outcomes (i.e. feasibility, fidelity, implementation cost, and reach) will be assessed to determine implementation effectiveness within groups. For the INT group following the completion of the intervention (at T2): (1) metrics will be captured by the Resource (e.g. user visits to the Resource, steps and relevant tasks completed, time interacting with each Step of the Resource and related activities, and expenses associated with these activities); and [2] focus group interviews will be conducted with members of the Change Team. For the SP group who elect to complete the six-month implementation of the Resource, implementation outcomes will be assessed using the same metrics captured by the Resource, as described above. No focus group interview will be undertaken for the SP group.

Sustainability will be assessed at T3 and T4 for INT group, and at T4 for SP group (See Table 1) through data retrieved from medical charts and metrics captured by the Resource.

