### Data management, analyses, and monitoring

#### Quantitative data

All primary analyses to determine intervention effectiveness will be conducted as intention to treat. The characteristics of infants admitted to participating NICUs and enrolled in the study will be summarized using descriptive statistics such as means and SD for continuous variables and medians and ranges for categorical variables. Given the lack of independence in outcomes due to sampling of multiple patients from the same NICU, inferential statistical methods that account for this clustering will be used. To assess the impact of the Resource on the clinical outcomes (proportion of infants with any validated pain assessment used and any pain management strategy used), the odds of a particular outcome will be compared between INT and SP groups as the odds ratio with 95% confidence interval and *p* value. Parameter estimation will be facilitated by a logistic regression model, with the clustering by NICU accomodated by estimation using Generalized Estimating Equations. The impact of contextual factors on clinical outcomes will be explored. Generalized estimating equation models for binary outcomes (i.e. logit link) will model implementation outcomes in both groups while including contextial covariates. All models will be assessed for goodness-of-fit. Imputation for missing data will be employed only if there is > 10% of missing data. Comprehensive training and database monitoring will be performed to minimize potential loss of data; in a previous study in which similar data was collected [16], missing data were minimal (< 5%). All analyses will be conducted using SAS v9.4 (Cary, NC, USA).

Analysis of implementation costs will be captured within Resource metrics which include quantifying resources required for its implementation over a six-month period—including: human resources (time spent on orientation and training, navigation through the Resource, meetings among Change Team members, implementation of the Resource either individually or in groups); equipment (e.g. laptop); materials (e.g. printing materials); and other related expenses—and will be captured by the Resource (Steps 5 and 7). The uncertainty of the findings will be explored. This analysis can provide evidence to inform scalability and sustainability of the Resource.

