For organizational context data, descriptive statistics (e.g. means, SD) for each of the 10 ACT concepts will be reported. Outcome means for each NICU will be compared to the overall sample. We will also categorize the NICUs in a binary manner as high or low using quartiles. Analysis of variance and multiple comparison tests will be used to investigate differences in workplace environment characteristics relative to primary outcomes. If an adequate sample size is not achieved, then non-parametric methods (e.g. Kruskal–Wallis test) will be used. Regression modeling will be used to assess the influence of organizational factors on clinical pain practices to determine if units with more positive organizational context scores are more successful in adopting the resource and have more positive pain management practices.

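### Binary-logit GEE is assigned to implementation outcomes without exception, but several are non-binary with one value per NICU, and the high/low context split by quartiles is undefined

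*Protocol article*

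**What the plan says.** The Quantitative data section, under Data management, analyses, and monitoring, gives one model for the whole family of implementation outcomes: "Generalized estimating equation models for binary outcomes (i.e. logit link) will model implementation outcomes in both groups while including contextial covariates". It names no exception.

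Table 1 defines those outcomes as follows:

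- **Feasibility:** "Focus group. A semi-structured interview guide was developed according to CFIR constructs", collected at T2 in the intervention (INT) group. The Implementation (secondary) outcomes section adds for the standard practice (SP) group: "No focus group interview will be undertaken for the SP group".
- **Fidelity:** progress through the seven steps, where "completeness of included information will be considered the metric for fidelity".
- **Implementation cost:** "The financial and time cost to implement the Resource".
- **Reach:** "Proportion (%) of NICU staff who receive a KT strategy", over the staff who should have received it.
- **Sustainability:** two parts. One is maintained effectiveness, taken from infant charts. The other is "Duration (in months) that NICU continues to use the ImPaC Resource with fidelity".

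On organizational context, the Quantitative data section reports means and SDs for the 10 Alberta Context Tool (ACT) concepts and then says: "We will also categorize the NICUs in a binary manner as high or low using quartiles". It also plans analysis of variance against the primary outcomes, and a regression of clinical pain practices on organizational factors.

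Specific secondary objectives and Study design present the implementation aim as descriptive and within-group. Other objectives makes the context aim exploratory, covering both clinical and implementation outcomes.

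**The concern.** A logit model needs a yes/no response or a count of successes out of a known number. GEE is useful when several responses share a cluster. Several of the listed outcomes meet neither condition as defined. To run the stated model on them, someone would have to choose a cut-point for months of use, for cost, or for overall progression and completeness. The article states none, so the choice could be made after the data are seen.

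The context split adds a second undefined cut. Four quarters do not by themselves give two groups, and the possible readings use different units and can give different answers.

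At stake is the implementation half of the context objective. The logit GEE is the only model expressly assigned to implementation outcomes. The later regression names clinical pain practices as its outcome, although its stated aim also mentions adoption of the Resource.

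**Working it through.** **1. The plan's own figures (Sample size).** Inputs: 30 charts per NICU, intraclass correlation 0.2, 16 NICUs (8 per arm assumed), 80% power, two-sided 5%, 10% site dropout.

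- Design effect: 1 + (30 − 1) × 0.2 = 6.8.
- Effective infants per arm: 8 × 30 / 6.8 = 35.3.
- Detectable difference: (1.960 + 0.842) × √(2/35.3) = 0.667 SD, against 0.67 stated.
- Units to enrol: 16 / 0.90 = 17.8, so 18.

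These reproduce. They concern the chart outcomes; what carries over here is the number of units, 16 to 18.

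**2. Each implementation outcome against the stated model.**

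| Outcome in Table 1 | Form of the data | Binary-logit GEE in both groups? |
|---|---|---|
| Feasibility (focus group) | Qualitative, INT only | No |
| Fidelity, overall progression and completeness | Graded, one value per team | No, without an unstated cut-point |
| Fidelity, each step done or not | Up to seven yes/no items per NICU | Possible |
| Cost | Money and time per NICU | No, without an unstated cut-point |
| Reach | Staff reached out of staff expected | Yes, as grouped binomial |
| Sustainability, charts | Yes/no pain practices in 30 infants per NICU | Yes |
| Sustainability, months of use | One duration per NICU | No, without an unstated cut-point |

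**3. Clustering.** With one value per NICU the cluster size is 1, and 1 + (1 − 1) × ICC = 1 whatever the ICC. GEE then amounts to ordinary regression with robust standard errors on at most 18 points (about 9 INT units at T2 and 9 SP units at T3, fewer if some SP units decline the Resource). The section's reason for clustered methods, several patients sampled from one NICU, does not apply to these outcomes.

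**4. What 16 to 18 units can show about context.** For a continuous score, the smallest correlation detectable with 80% power at two-sided 5% is r = tanh[(1.960 + 0.842)/√(n − 3)]:

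- n = 18: tanh(0.723) = 0.62
- n = 16: tanh(0.777) = 0.65
- n = 9 (one group): tanh(1.144) = 0.82

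For a high/low comparison of 18 units, the detectable difference d comes from a noncentral t with n₁ + n₂ − 2 degrees of freedom and noncentrality d/√(1/n₁ + 1/n₂). The text allows at least three readings:

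- median split, 9 v 9: 1.41 SD
- top quarter v rest, 5 v 13: 1.57 SD
- top v bottom quarter, 4 v 5: 2.19 SD, leaving out about half the units. These groups lie further apart on the score, so this figure is not directly comparable with the first two.

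**5. Information lost by splitting, if the score is normal.**

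- Median split: correlation with the score √(2/π) = 0.80; information kept 2/π = 0.64. That is worth about 18 × 0.64 = 11.5 units.
- Top quarter v rest: correlation 0.318/√(0.25 × 0.75) = 0.73; information kept 0.73² ≈ 0.54.

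**The case against.** Much of the case on the other side stands.

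- **Several outcomes do fit.** Reach is a staff proportion, chart-based sustainability is the usual logit-GEE setting, and step completion can be read as clustered yes/no items. A reader might infer that almost no implementation outcome suits the model; Table 1 does not support that. For reach and steps completed, a quasi-binomial model would be close to what is planned.
- **Cost and feasibility have their own analyses.** Cost has a separate paragraph in the Quantitative data section, and focus groups have directed content analysis under Qualitative data. In practice, neither need be forced through a logit. Even so, the model sentence makes no exception, and neither of those passages relates the outcome to context by a model.
- **The ten ACT concepts are never said to enter one model.** A reader might infer 18/10 = 1.8 units per covariate and models that cannot be fitted. In simulations with a binary unit-level outcome at 50% and independent covariates unrelated to it, separation occurred in about 82% of data sets with ten covariates and 18 units, but in almost none with a single covariate. The problem depends on joint entry, which the article does not state.
- **The split is an addition.** Concept scores are still reported, and the aim of the regression is worded in terms of scores. Context is not simply reduced to high or low.
- **Some detail belongs elsewhere.** The link function for each secondary outcome is commonly left to a fuller document. That would excuse silence. Here the article states one method for all the outcomes, and it conflicts with the article's own definitions of several of them.

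**Conclusion.** The point holds in limited form. The stated model does not match months of use, cost, or fidelity as overall progression and completeness, and it cannot apply to focus-group feasibility in both groups. It remains suitable for reach, chart-based sustainability and item-level step completion. The quartile split is undefined and, whichever reading is taken, discards information from a sample of only 16 to 18 units. The 64% figure assumes a median split of a normal score, neither of which the article states.

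It would be tempting to conclude that the context objective cannot be answered. The documents do not support this: its clinical part rests on infant-level data and a separate regression, and the aim is exploratory. The primary effectiveness comparison is unaffected. The gap is worth correcting because the correction is cheap and removes the room for cut-points chosen after the fact.

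**What to change.** Replace the single sentence on implementation outcomes with a method matched to each outcome:

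- **Infant-level binary data (chart-based sustainability):** keep logit GEE clustered by NICU.
- **Reach and steps completed out of seven:** binomial-type logit model with allowance for overdispersion.
- **Cost:** NICU-level analysis on the log scale.
- **Months of use:** NICU-level analysis on its own scale. INT units are followed for 12 months after the intervention and SP units for six, so summarise within group or to a common horizon.
- **Completeness of information:** describe at NICU level as a graded measure, without a cut-point.
- **Focus-group feasibility:** leave to the qualitative analysis, INT only.
- **Context:** enter ACT scores as continuous, one at a time, and report estimates with 95% confidence intervals, labelled exploratory.
- **Quartile split:** drop it, or define the two groups in advance and use them for description only.

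The cost is a change of wording, with no new data. The estimates will be imprecise with at most 18 units, but that limit comes from the number of NICUs and applies under any method.

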To increase effective implementation of knowledge to practice, we developed the Implementation of Infant Pain Practice Change (ImPaC) Resource (Resource). The goal of this web-based multifaceted implementation strategy is to support change in the pain practice behaviors of healthcare professionals (HCP). The Resource uses a standardized seven-step approach that guides developing a change team, measuring readiness for change, assessing current pain practices, reviewing current evidence, developing an aim statement, providing implementation strategies and templates for utilization in the practice setting, and enabling audit and progress monitoring. The Resource builds on previous findings on the evaluation of a real-time multifaceted implementation intervention “Evidence-based Practice for Improving Quality” (EPIQ) involving 32 hospital units within eight Canadian pediatric hospitals [15, 16]. The EPIQ intervention incorporated high-quality evidence and quality improvement (QI) methods using interactive knowledge translation (implementation) strategies (e.g. reminders, education, educational outreach, and audit and feedback). The 16 units that received the EPIQ intervention demonstrated statistically significant improved pain practices and clinical outcomes for hospitalized children when compared to the 16 units that continued with standard practices [16]. Organizational context influenced clinical outcomes [15] but EPIQ was not always considered feasible or cost-effective [17] and results were only partially sustained over 12–36 months [15, 16]. To address these limitations, the Resource was designed as a user-friendly, universally available, self-administered web-based tool to support hospital-based change agents.

This protocol describes the development, implementation, and evaluation of the Resource. The study was informed by the Consolidated Framework for Implementation Research (CFIR) that details key constructs associated with implementation success [18] and Proctors’ Implementation Outcome Taxonomy [19]. The usability of the Resource was tested with end-users in non-clinical scenarios and clinical situations and was demonstrated to be feasible, acceptable, comprehensive, and trustworthy [20, 21].

The goal of this study is to evaluate the effectiveness and the implementation of the Resource and explore the association of organizational context with clinical and implementation outcomes.

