### Other objectives

To explore the influence of organizational context on clinical and implementation outcomes.

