### Standard Practice (SP) group

The SP group will continue as usual with their unit or institutional pain practices. Any implementation strategies implemented organizationally (e.g. new staff orientation) will be noted. The SP group will be offered the Resource following T2 outcome evaluations (e.g. six months after randomization) and be invited to utilize the Resource in a similar manner and time as the INT group. Sustainability data will be collected at six months after intervention completion (Table 1).

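### A regression of pain practice on organizational context is used to judge success in adopting the Resource, but it cannot separate uptake from practice already in place

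*Protocol article*

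**What the plan says.** The last sentence of the organizational context paragraph (Protocol article, Data management, analyses, and monitoring, Quantitative data) names an outcome, a predictor and a purpose. The analysis is "Regression modeling will be used to assess the influence of organizational factors on clinical pain practices" and its purpose is "to determine if units with more positive organizational context scores are more successful in adopting the resource and have more positive pain management practices". The sentence gives no time point, set of units, T1 adjustment or arm-by-context term.

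Other parts of the article bear on how to read it:

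- The preceding paragraph of the same section says "The impact of contextual factors on clinical outcomes will be explored", and that generalized estimating equation models "will model implementation outcomes in both groups while including contextial covariates".
- Table 1 lists fidelity (progress through the seven steps) and reach (share of staff receiving a strategy) among the implementation outcomes. Both come from the back end of the website, at T2 for the intervention (INT) group and T3 for the standard practice (SP) group.
- Clinical outcomes are collected at T1 and T2 in both groups, and staff nurses complete the Alberta Context Tool (ACT) at T1.
- On access: "The SP group will be offered the Resource following T2 outcome evaluations".
- The objective is listed under Other objectives: "To explore the influence of organizational context on clinical and implementation outcomes".

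**The concern.** The null hypothesis of the stated regression is that context is unrelated to the level of documented pain practice. The null hypothesis behind the first conclusion is that context is unrelated to how well a unit takes up the Resource. These are different hypotheses. A unit with good context may already assess and treat pain more often at T1. If so, it will probably still do so at T2, in either arm, and the context coefficient will be non-zero even if uptake is the same in every unit.

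The design makes the gap plain. At T1 no unit has the Resource, and at T2 about half the units still have no access to it. A context-practice association among SP units at T2 cannot reflect adoption, yet it would feed a pooled context coefficient.

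At stake is the advice on implementing the Resource in different organizational contexts, which the abstract's Discussion says the results will inform. The trial could report that context drives success with the Resource after showing only that better-context units had better practice. It could also miss a real modification of the effect if the pre-existing association runs the other way.

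**Working it through.** **The plan's own figure first.** The Sample size section gives 30 records per NICU, ICC 0.2, 16 NICUs and a difference of 0.67 SD. Variance inflation = 1 + (30 − 1) × 0.2 = 6.8. Effective n per arm, taking 8 NICUs per arm, = 8 × 30 / 6.8 = 35.3. Power at 0.67 SD, two-sided 5%, is 80.4%, against the stated 80%. The figure reproduces. It concerns the arm comparison; no figure is given for the context analysis.

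**Illustration for the context regression.**

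- From the article: 18 NICUs (taken as 9 per arm), 30 records per time point, ICC 0.2, arm effect 0.67 SD.
- Assumed, not in the article: a continuous outcome with total SD 1; 80% of between-NICU variance persisting from T1 to T2; and a correlation r between context (SD 1) and the persistent part of NICU practice.
- Under the null, context has no bearing on the effect of the Resource.

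**Expected slopes.** The persistent between-NICU SD is √(0.2 × 0.8) = 0.4, so the expected context slope at T2 is 0.4r in each arm. At r = 0.5 it is 0.20. The variance of a NICU mean is 0.2 + 0.8/30 = 0.227. After removing 0.20² = 0.04, the residual is 0.187, SD 0.43. The standard error of the pooled slope is roughly 0.43/√18 = 0.10, so the coefficient sits about 2 standard errors from zero although context has nothing to do with uptake. The arm-by-context interaction has expectation 0.4r − 0.4r = 0 at any r.

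**Simulated rejection at nominal 5% under that null** (NICU-level regressions, 4,000 to 8,000 replicates; ranges span repeat runs):

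| Analysis | r = 0 | 0.3 | 0.5 | 0.7 |
|---|---|---|---|---|
| T2 practice on context + arm, all units | 5% | 16-17% | 39-40% | 72-74% |
| T2 practice on context, INT units only | 5% | 10% | 20% | 40-42% |
| Arm-by-context interaction | 5% | 5% | 5% | 4-5% |
| T1-to-T2 change on context, INT units only | 5% | 5% | 5% | 5% |

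Restricting to INT units does not remove the problem. An arm contrast or use of T1 does.

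**When context does change the benefit.** Suppose the benefit rises by 0.33 SD per SD of context (assumed). The pooled slope is then 0.33/2 + 0.4r: 0.165 at r = 0, 0.045 at r = −0.3 and −0.035 at r = −0.5. At the two negative values it nearly cancels. Simulated power of the context coefficient is 25% at r = 0 and 7-8% at r = −0.3 and −0.5. It is 57% at r = 0.3 and 80% at r = 0.5, but much of that is the pre-existing association. The interaction adjusted for the T1 NICU mean has 36-39% power at all of these values of r.

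**The case against.** The strongest reply is that adoption has its own planned analysis. The implementation-outcome models with context covariates cover fidelity and reach, which measure use of the Resource directly and do not depend on charting habits before the trial. This stands. A reader might infer that the practice regression is the only planned route to the adoption question, and the article does not support that. What remains is that the context paragraph attaches the adoption conclusion to clinical practices and does not refer to those models.

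Second, the sentence has two aims, and regressing practices on context is a fair analysis of whether better-context units have more positive practices. For that aim the rejections in the table are correct detections of a real association. This also stands; the defect is confined to the first aim.

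Third, the article is condensed. A reader might infer that the sponsor rejected an arm-by-context or T1-adjusted analysis, but the text only leaves it unstated, and the full protocol or SAP may contain it. Added model terms alone would still leave the published sentence drawing an adoption conclusion from a practice outcome.

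Fourth, r and the 80% persistence are assumptions. The Background says of the earlier programme "Organizational context influenced clinical outcomes", and one might take this to show that a pre-existing association is likely. It does not: the remark fits effect modification equally well.

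Finally, an arm-by-context interaction on clinical outcomes does not measure adoption either. A unit can use the Resource fully with little change in its charts. The repair therefore has to treat adoption and clinical benefit separately.

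**Conclusion.** The point holds in a limited form. The organizational context paragraph draws a conclusion about success in adopting the Resource from a regression whose named outcome is clinical pain practice, and a context main effect on that outcome cannot support it. The chance of a misleading positive runs from about 5% at r = 0 (no inflation) to 72-74% at r = 0.7, for T2 data pooled over arms with 80% of between-unit variance persisting. The article supplies neither assumption and does not fix the model, so these figures show the mechanism and are not a forecast. Context is an exploratory objective, and the randomized comparison of the primary outcomes and the sample size are untouched. This is a minor-to-moderate point.

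**What to change.** Reword the last sentence of the organizational context paragraph into three parts:

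1. **Adoption.** Judge it by the already planned models of fidelity and reach on context, in units while they have access to the Resource (INT up to T2, SP from T2 to T3).
2. **Clinical benefit.** Judge whether context changes it by an arm-by-context interaction on the T2 outcome, with the staff-nurse ACT score kept continuous, adjustment for the NICU's T1 value, and clustering by NICU. Report the interaction with its 95% confidence interval, labelled exploratory and imprecise with 16-18 units.
3. **Association.** Report the plain regression of practices on context as an association with practice level only.

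This changes analysis wording only. T1 and T2 clinical outcomes, staff-nurse ACT scores and website metrics are already to be collected in both groups. The cost is an imprecise interaction estimate: in the illustration, power is only 36-39% for a modification of 0.33 SD per SD of context.
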